**Fig. 2 Fig2:**
[figure not shown]
Institutional standardized systematic 12-core prostate biopsy mapping scheme. The standardized scheme for 12-core systematic biopsy (SB) of the prostate used in the DEPROMP Trial. Due to standardized SB, cores 1/2/3/7/8/9 are representative of the areas PZpl, and cores 4/5/6/10/11/12 are representative of the areas CZ and PZpm defined by PIRADS v2.1 sector map [1]

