**Fig. 1 Fig1:**
[figure not shown]
Annotation of suspicious lesions on imaging. **A**–**C** Concordant positive findings of clinically significant prostate cancer (csPCA) in the peripheral zone of the right prostate lobe on multiparametric magnetic resonance imaging (MRI) and gallium-68 prostate-specific membrane antigen positron emission tomography/computed tomography (PSMA-PET/CT). In the DEPROMP Trial, uro-radiologists (**A**, **B**) and nuclear medicine physicians (**C**) annotate defined suspicious lesions in imaging layers to enable effective and clear interdisciplinary communication before targeted biopsy (TB) as demonstrated in exemplary fashion. An example of a false-negative MRI with true-positive PSMA-PET/CT in the posterior transitional zone of the left prostate lobe is shown in series **D**–**F**. The PSMA-PET/CT-guided TB detected a solitary, Gleason 3 + 4 PCA. In both cases, radical prostatectomy confirmed the risk stratification based on biopsy yields

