##### Prostate biopsy

The same physician performs SB and MR- and PET-targeted biopsies in one session. A pre-defined, software-assisted template is used for the institutional standardized biopsy in all participants. Due to standardization, cores 1/2/3/7/8/9 represent the outer peripheral posterolateral zone, and cores 4/5/6/10/11/12 represent the outer peripheral posteromedial zone and the central zone defined by PIRADS v2.1 sector map (Fig. 2). Biopsies will be conducted under antibiotic prophylaxis, rectal cleansing, and local anesthesia. Targeted tissue sampling will be performed from the areas classified as tumor-suspicious by MRI (PI-RADS ≥ 3) and/or PSMA-PET/CT (miPSMA ≥ 1). Up to three identified lesions on PSMA-PET/CT and/or MRI will be targeted with three biopsies per target. Software-assisted fusion technique (KOELIS Trinity®) is used for both SB and image-guided biopsies. Targeted samples are color-coded to allow for subsequent differential analysis. All biopsies are separately documented and sent for histopathological analysis.

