#### Secondary outcomes

The following are the secondary outcomes of the study:To determine the additive value of PET/MR-TB for detecting csPCA in men undergoing initial biopsy for suspected PCA compared to SOCTo determine the sensitivity, specificity, PPV, NPV, and diagnostic accuracy for PCA and csPCA of MRI, PSMA-PET/CT, biopsy modalities (SB vs. MR-TB vs. PET-TB vs. PET/MR-TB), and the respective imaging classifications (PIRADS V2.1 classification, PROMISE miTNM classification V1.0, miPSMA score)To determine the additive value of more than one targeted biopsy per MRI- or PSMA-PET/CT suspicious lesionTo determine the concordance of tumor burden defined preoperatively by MRI and PSMA-PET/CT and tumor extent in the prostatectomy specimen using whole-mount sectionsTo determine the frequencies of predefined adverse events CTCAE grade 3 in the context of PET/MR-TB in relation to the total number of biopsy cores taken and anticoagulants intakeTo determine the concordance of biomarker expression (PTEN and PSMA) between tumor-bearing prostate specimens (biopsy cores vs. prostatectomy specimens) and concordance between PSMA expression of PSMA-PET/CT imaging and prostatectomy specimens and tumorous lymph nodes

The timing of measurements of outcomes a–c and e will occur after histopathologic analysis of the prostate biopsy and completion of study visit 4 (appropriately defined as study day 21).

The timing of measurements of outcomes d and f will occur after histopathologic analysis of prostatectomy specimens and completion of study visit 5 (appropriately defined as study day 180).

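### The systematic cores leave the transition and anterior zones unverified unless a scan flags them, so biopsy-referenced sensitivity and NPV of imaging are biased upward

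*Protocol article*

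**What the plan says.** The protocol article describes the template twice. The Fig. 2 legend says that "cores 1/2/3/7/8/9 are representative of the areas PZpl, and cores 4/5/6/10/11/12 are representative of the areas CZ and PZpm". The text under Visit 3, Prostate biopsy, agrees: "cores 1/2/3/7/8/9 represent the outer peripheral posterolateral zone, and cores 4/5/6/10/11/12 represent the outer peripheral posteromedial zone and the central zone". The scheme is the same for every man: "A pre-defined, software-assisted template is used for the institutional standardized biopsy in all participants".

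Other tissue comes from imaging targets only. The same section says that "Targeted tissue sampling will be performed from the areas classified as tumor-suspicious by MRI" at PI-RADS 3 or higher, by PSMA-PET/CT at miPSMA 1 or higher, or by both. It adds a cap: "Up to three identified lesions on PSMA-PET/CT and/or MRI will be targeted with three biopsies per target".

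The second listed secondary outcome (b in the timing sentence) covers sensitivity, specificity, predictive values and accuracy of MRI, PSMA-PET/CT and the biopsy methods. On timing, the section Secondary outcomes says: "The timing of measurements of outcomes a–c and e will occur after histopathologic analysis of the prostate biopsy", with visit 4 at about day 21. Prostatectomy follows on days 22 to 180 (Participant timeline), only in some men, and its histology sets the timing for outcomes d and f.

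**The concern.** For imaging accuracy, the reference standard should be applied in the same way whatever the scan shows. Here that holds only in the regions the template samples. Outside them, whether tissue is taken depends on the tests under evaluation.

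The protocol's own example shows the mechanism. The Fig. 1 legend presents "An example of a false-negative MRI with true-positive PSMA-PET/CT in the posterior transitional zone of the left prostate lobe", a Gleason 3 + 4 tumour found by the PET-targeted biopsy. The MRI miss came to light because PET flagged the spot. Had PET also been negative there, no planned core was assigned to that zone and the miss could have gone unrecorded.

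The error runs in one direction and favours imaging. The estimates affected are those a reader would use to judge how safe a negative scan is. The limitations in the Discussion do not mention this, and the statistical methods section plans plain estimates with 95% confidence limits.

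**Working it through.** **Plan's own figure.** The plan gives no figure on this point. Its one precision figure concerns the primary outcome and reproduces: 1.96 × √(0.25/200) = 6.93%, against the stated ± 6.9%. The present point does not touch it.

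**Coverage.** Cores 1/2/3/7/8/9 are six and cores 4/5/6/10/11/12 are six, so 6 + 6 = 12. Every systematic core is assigned to PZpl, PZpm or CZ, and none is left for the transition zone or the anterior areas.

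**Which cancers stay hidden.** A cancer outside the sampled regions is unverified if MRI is below PI-RADS 3 and PET is miPSMA 0. At patient level this changes the classification only when no csPCA is found elsewhere.

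**Patient-level model.** Let π be the prevalence of csPCA, sp the MRI specificity, sM and sP the sensitivities of MRI and PET at the targeting thresholds, and q the share of men with csPCA whose csPCA lies only in unsampled zones. Targeted cores are taken to find every flagged cancer.

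- Hidden share of csPCA men, independent misses: h = q(1 − sM)(1 − sP)
- Hidden share if PET misses everything MRI misses: h = q(1 − sM)
- Apparent MRI sensitivity = sM / (1 − h)
- True NPV = (1 − π)sp / [(1 − π)sp + π(1 − sM)]
- Apparent NPV = [(1 − π)sp + πh] / [(1 − π)sp + π(1 − sM)]

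**Inputs.** The MRI sensitivity of 88% is the figure cited in Background and rationale. All else is assumed: sM of 70% as an alternative, sP 70% or 90%, q 5 to 30%, π 40 to 50%, sp 50%.

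**Small end** (sM 0.88, sP 0.90, q 0.05, π 0.40):
- Independent: h = 0.05 × 0.12 × 0.10 = 0.0006. Sensitivity goes from 0.880 to 0.8805. NPV goes from 0.300/0.348 = 0.862 to 0.30024/0.348 = 0.863.
- PET misses all MRI misses: h = 0.05 × 0.12 = 0.006. Sensitivity 0.8853, NPV 0.3024/0.348 = 0.869.

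**Large end** (sM 0.70, sP 0.70, q 0.30, π 0.50):
- Independent: h = 0.30 × 0.30 × 0.30 = 0.027. Sensitivity goes from 0.700 to 0.7194. NPV goes from 0.250/0.400 = 0.625 to 0.2635/0.400 = 0.659.
- PET misses all MRI misses: h = 0.30 × 0.30 = 0.09. Sensitivity 0.7692, NPV 0.295/0.400 = 0.737.

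| Rise in points | Independent misses | PET misses all MRI misses |
|---|---|---|
| MRI sensitivity | about 0.1 to 2 | about 0.5 to 7 |
| MRI NPV | about 0.1 to 3 | about 0.7 to 11 |

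With the cited 88%, sP 70% and q 10 to 30%, the independent case gives an apparent sensitivity of 88.3 to 89.0%. For MRI and PET combined at the targeting thresholds, the independent case moves 98.8% to 98.9% at the small end and 91.0% to 93.5% at the large end.

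**The case against.** The strongest reply is that the effect is small and concerns a descriptive secondary outcome in an exploratory study. With independent misses, most of what MRI overlooks is exposed by PET targets. Sampling error would also often be larger: with 200 men, sensitivity 88%, an assumed specificity of 60% and prevalence of 30% or 50%, about 91 or 72 men are test-negative. The 95% half-width for NPV is then about 5.5 or 8.6 points. This stands as a limit on importance. It does not remove the bias, because a confidence interval does not reflect a one-sided error, and independence of misses is itself unverified.

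Second, whole-mount comparison with preoperative imaging is already planned. That is so, but as concordance of tumour extent (outcome d), not as the reference for outcome b.

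Third, this might be detail left to a fuller document. The article itself fixes the template, the targeting trigger and the day-21 timing, and together these settle what the biopsy can verify.

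Fourth, Fig. 2 is not shown, and a core said to represent one area may cross another. That could soften the effect, but no core is assigned to the missing zones.

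Stronger readings are tempting and are not supported:
- A reader might infer that combined imaging is forced to 100% sensitivity and NPV in the unsampled zones. PET is rated positive at miPSMA 2 or higher but targeted at 1 or higher, so a cancer that is MRI-negative with miPSMA 1 is biopsied and can count as a verified miss.
- A reader might infer that a zone-by-zone comparison of MRI and PET against biopsy is distorted. No such analysis is stated: PET is evaluated per patient and per lesion, and sector mapping of histological extent is described for whole-mount specimens.
- A reader might infer that imaging NPV is the planned basis for reducing biopsies. The Discussion ties that to comparing risk stratification between biopsy methods.

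**Conclusion.** The point holds as a bias of known direction and unknown size. As written, cancers outside PZpl, PZpm and CZ that both scans miss are not verified at biopsy, so biopsy-referenced sensitivity and NPV of MRI, PSMA-PET/CT and their combination are too high.

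The ranges in the table are illustrations. They rest mainly on the share of csPCA confined to unsampled zones, which the documents do not give and which may be small, and on how strongly MRI and PET misses coincide. They also ignore targeted cores that miss their lesion and flagged lesions beyond the cap of three. The upper figures need PET to miss every cancer MRI misses and should not be read as expected values.

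The primary outcome and its sample size are unaffected. The point is worth correcting because the remedy uses data the trial already collects.

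**What to change.** Leave the biopsy scheme as it is and amend the analysis of outcome b:

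1. Report patient-level sensitivity and NPV of imaging against biopsy as upper limits with respect to csPCA outside the template-sampled regions, and add this to the limitations.
2. If lesion- or region-level accuracy against biopsy is reported, count imaging-negative areas as true or false negatives only in PZpl and in CZ and PZpm taken together, since one set of cores stands for both. Elsewhere, report only PPV and the relative detection of MRI versus PET.
3. Add sensitivity and NPV of MRI and PSMA-PET/CT against the whole-mount sector maps in men who have prostatectomy, beside the biopsy-based values, with a caveat that these men are a selected subset.

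The cost is analysis wording and one further set of estimates. Core locations, sector maps and whole-mount sections are already part of the plan. The downside is fewer evaluable regions, and a whole-mount estimate that does not carry over directly to all men who had a biopsy.

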##### Histopathology

The analysis will be conducted according to the guidelines [4]. Specifically, specimens are labeled by location and, if applicable, whether they were obtained by SB, PET-TB, or MR-TB. Furthermore, the number of positive cores and the highest Gleason score per prostate lobe, per biopsy method, and per suspicious area (MRI and/or PSMA-PET/CT) are determined. Moreover, the loss of the tumor suppressor gene phosphatase and tensin homolog (PTEN) and PSMA expression will be determined in tumor-bearing biopsy specimens by immunohistochemistry. PSMA expression will be rated by an institutional-established valid semi-quantitative scale ranging from 0 to 3: “none,” “low,” “intermediate,” or “high,” respectively.

#### Visit 4

##### Risk stratification and conduct of management plan

Diagnosis and risk stratification will be based on histopathological analysis and imaging information. To reduce bias from natural variance in clinician recommendations, management plans will be conducted randomized and blinded by four independent specialists using institutional-based questionnaires (Additional file 1: Appendix). Participants will be allocated to either SOC- or SOC and PET-TB group for review. Hence, the reviewers will be presented with either all PET/MR-TB results or SOC biopsy results without PET-TB information. This results in four independently proposed management plans per patient.

#### Visit 5

##### Radical prostatectomy

Depending on the patient’s preference and tumor stage, active therapy (radical prostatovesiculectomy, radiotherapy, multimodal therapy) or active surveillance will be performed. Histopathology of prostatectomy specimens, if available, will be conducted using whole-mount specimens. Pathological tumor extent will be described in detail concerning spatial cancer expansion defined by PI-RADS v2.1 sector map. Tumor stage and grading will be compared to preoperatively defined tumor burden by imaging and biopsy results. In case of active surveillance, re-biopsy will be conducted following the DEPROMP protocol including additive PET-TB and analysis of biomarkers. In addition, a translational, exploratory analysis of biomarker expression in pre- and postoperative staging will be performed. PSMA expression of tumor-bearing prostate specimens (biopsy cores vs. prostatectomy specimens), tumorous lymph nodes, and initial PSMA-PET/CT imaging will be compared.

#### Criteria for discontinuing or modifying allocated interventions {11b}

On participants’ request interventions can be discontinued but not modified. All study data collected up to the point of patient withdrawal will be included in the final analysis.

#### Strategies to improve adherence to interventions {11c}

To improve adherence to intervention protocols, uniform work protocols were defined for radiologic and nuclear imaging, the biopsy procedure, and histopathologic evaluation of biopsy and prostatectomy specimens.

#### Relevant concomitant care permitted or prohibited during the trial {11d}

During the study, there are no restrictions on concomitant treatments and interventions. However, medications that have an anticoagulant effect or an impact on PSA levels will be documented.

#### Provisions for post-trial care {30}

Study-related health injuries are compensated with a maximum coverage of 500.000 euros per participant. The insurance covers possible injuries suffered by the participant directly or indirectly as a result of the use of study-related radiation applications or interventions in connection with the clinical trial.

Patients will be followed up after the biopsy by their urologist or on the study site depending on the patient’s preference for 2 years. PSA levels and PCA-specific diagnostic and therapeutic measures will be recorded quarterly. Afterwards, participants will continue to receive care from their urologist reimbursed by public and private health insurance.

### Outcomes {12}

The impact of PET/MR-TB on management intent is determined randomized by questionnaires evaluation after biopsy has been performed (Additional file 1: Appendix). Changes in management plans are any changes resulting from additional information obtained through PET-TB, including inter- and intra-modal adjustments. Diagnostic accuracy of significant cancer detection is determined using the definitions for csPCA with ISUP grade group ≥ 2. On-site radiologists will grade MRI according to PI-RADS version 2.1 [21]. PSMA-PET/CT images are evaluated per patient and per lesion according to the PROMISE miTNM classification system and the miPSMA expression score at the University Hospital Bonn [22]. PSMA expression will be rated by an established validated semi-quantitative analysis.

#### Primary outcome

The primary outcome is the proportion of men with suspected prostate cancer (PCA) in whom the management plans are changed by additive PSMA-PET/CT-guided prostate biopsy in combination with standard of care using systematic and MRI-guided biopsy compared with SOC alone. Treatment plans are performed randomized for each patient based on information obtained by SOC biopsy or combined PET/MR-TB using questionnaires within 21 days of biopsy. The proposed treatment plans will be compared at intramodal and intermodal levels, and the number of patients with modified treatment regimens will be determined.

#### Secondary outcomes

The following are the secondary outcomes of the study:To determine the additive value of PET/MR-TB for detecting csPCA in men undergoing initial biopsy for suspected PCA compared to SOCTo determine the sensitivity, specificity, PPV, NPV, and diagnostic accuracy for PCA and csPCA of MRI, PSMA-PET/CT, biopsy modalities (SB vs. MR-TB vs. PET-TB vs. PET/MR-TB), and the respective imaging classifications (PIRADS V2.1 classification, PROMISE miTNM classification V1.0, miPSMA score)To determine the additive value of more than one targeted biopsy per MRI- or PSMA-PET/CT suspicious lesionTo determine the concordance of tumor burden defined preoperatively by MRI and PSMA-PET/CT and tumor extent in the prostatectomy specimen using whole-mount sectionsTo determine the frequencies of predefined adverse events CTCAE grade 3 in the context of PET/MR-TB in relation to the total number of biopsy cores taken and anticoagulants intakeTo determine the concordance of biomarker expression (PTEN and PSMA) between tumor-bearing prostate specimens (biopsy cores vs. prostatectomy specimens) and concordance between PSMA expression of PSMA-PET/CT imaging and prostatectomy specimens and tumorous lymph nodes

The timing of measurements of outcomes a–c and e will occur after histopathologic analysis of the prostate biopsy and completion of study visit 4 (appropriately defined as study day 21).

The timing of measurements of outcomes d and f will occur after histopathologic analysis of prostatectomy specimens and completion of study visit 5 (appropriately defined as study day 180).

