**Secondary study objectives**
➢ To determine the additive value of PET/MR-TB for detecting csPCA in men undergoing initial biopsy for suspected PCA compared to SOC
➢ To determine sensitivity, specificity, PPV, NPV, and diagnostic accuracy for PCA and csPCA of MRI, PSMA-PET/CT, biopsy modalities (SB vs. MR-TB vs. PET-TB vs. PET/MR-TB), and the respective imaging classifications (PIRADS V2.1 classification, PROMISE miTNM classification V1.0, miPSMA score)
➢To determine the additive value of more than one targeted biopsy per MRI- or PSMA-PET/CT suspicious lesion
➢ To determine the concordance of tumor burden defined preoperatively by MRI and PSMA-PET/CT and tumor extent in the prostatectomy specimen using whole-mount sections
➢ To determine the frequencies of predefined adverse events CTCAE grade 3 in the context of PET/MR-TB in relation to the total number of biopsy cores taken and anticoagulants intake
➢ To determine the concordance of biomarker expression (PTEN and PSMA) between tumor-bearing prostate specimens (biopsy cores vs. prostatectomy specimens) as well as concordance between PSMA expression of PSMA-PET/CT imaging and prostatectomy specimens and tumorous lymph nodes

*PET* Positron-emission tomography, *PET-TB* ultrasound-guided PSMA-PET/CT fusion biopsy, *SOC* Standard of care, *SB* Systematic 12-core ultrasound biopsy of the prostate, *MR-TB* ultrasound-guided MRI fusion biopsy, *PET/MR-TB* combined SB + MR-TB + PET-TB, *PCA* Prostate cancer, *csPCA* clinically significant prostate cancer, defined as PCA with Gleason score ≥ 7a, *PPV* Positive predictive value, *NPV* Negative predictive value, *MRI* Multiparametric magnetic resonance imaging, *PI-RADS* Prostate Imaging-Reporting and Data System, *PSMA* Prostate-specific membrane antigen, *PROMISE* Prostate Cancer Molecular Imaging Standardized Evaluation, *miTNM* molecular imaging TNM system, *miPSMA score* molecular imaging PSMA expression score, *CTCAE* Common Terminology Criteria for Adverse Events

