### Participant timeline {13}

Screening for eligibility will be performed on day 50 to 10 days before prostate biopsy. Imaging by transrectal US, MRI, and PSMA-PET/CT will be performed within 1–49 days before the procedure. Histopathology of prostate biopsy specimens and risk stratification (based on imaging results and histopathology) will be performed on days 1–21. If patients are applicable and do request radical prostatectomy, the procedure will be performed risk-adapted within 22–180 days after prostate biopsy. PSA levels will be determined quarterly for 2 years, and PCA-specific diagnostic and therapeutic measures will be recorded. The timeline of the study and assessments are given in Figs. 3 and 4.

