## Statistical methods

### Statistical methods for primary and secondary outcomes {20a}

The data collected and derived during the course of the trial will generally be presented in individual patient listings (sorted by site) and in corresponding summary tables. The summary tables will be displayed by time of assessment, if appropriate. Continuous variables will be summarized by the following statistics: number of observations, arithmetic mean, median, standard deviation (SD) minimum, and maximum. Summaries of categorical variables will show the absolute and relative frequencies by category and time of assessment. The primary endpoint will be evaluated showing the number and percentage of subjects with changing therapy algorithms due to new information through additional PET-TB together with 95% confidence limits. Secondary endpoints will be summarized descriptively. Sensitivity, specificity, and predictive values will be calculated including 95% confidence limits. Missing data are not replaced by imputation or other measures.

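### Biopsy-method accuracy is timed to day 21, when the study's own cores are the only histology, so PET/MR-TB scores 100% on every measure, and the other methods 100% on specificity and PPV, by construction

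*Protocol article*

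**What the plan says.** Table 1 and the Secondary outcomes section both ask for sensitivity, specificity, PPV, NPV and "diagnostic accuracy for PCA and csPCA of MRI, PSMA-PET/CT, biopsy modalities (SB vs. MR-TB vs. PET-TB vs. PET/MR-TB". PET/MR-TB is defined under Table 1 as the combination of SB, MR-TB and PET-TB, that is, all cores. The section Prostate biopsy has them taken in one session.

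The Secondary outcomes section then fixes the timing: for outcomes a to c and e, measurement "will occur after histopathologic analysis of the prostate biopsy and completion of study visit 4", given as study day 21. By list order, accuracy is outcome b. For the prostatectomy-based outcomes it says: "The timing of measurements of outcomes d and f will occur after histopathologic analysis of prostatectomy specimens and completion of study visit 5", given as study day 180. Participant timeline {13} adds that, for men who have a prostatectomy, "the procedure will be performed risk-adapted within 22–180 days after prostate biopsy".

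The analysis section {20a} promises: "Sensitivity, specificity, and predictive values will be calculated including 95% confidence limits". No section of the article names the reference standard for outcome b.

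**The concern.** An accuracy measure needs a reference that is not the test itself. At day 21 the only histology is the set of cores from the single biopsy session, and that set is one of the four tests compared.

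The article's Discussion says the comparison by method should help to judge whether multiple biopsies are needed. On the stated timing the combined approach would come out as perfect whatever its real performance, with confidence limits that look like evidence. The Background itself expects a sampling error in about one-third of patients even with SB and MR-TB combined, so disease missed by biopsy is a real possibility.

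**Working it through.** **The plan's own figure.** The only precision figure in Sample size {14} concerns the primary endpoint: 1.96 × √(0.5 × 0.5 / 200) = 6.93%, which reproduces the stated ±6.9%. The article gives no figure for the accuracy outcome.

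**Step 1: which reference is possible.** Outcome b is read at day 21 and prostatectomy starts at day 22. Only the study's cores remain. Take the reference R as positive if the highest grade over all cores reaches the threshold (any PCA: ISUP ≥ 1; csPCA: ISUP ≥ 2).

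**Step 2: the identities.**
- PET/MR-TB is positive exactly when R is positive. So FP = FN = 0, and sensitivity, specificity, PPV, NPV and accuracy are all 100%.
- For SB, MR-TB, PET-TB or SOC (SB + MR-TB), a positive core is also one of the cores in R. So FP = 0, and specificity and PPV are 100%.
- Enumeration check: 6 × 6 × 6 = 216 combinations of ISUP grade (0 to 5) for the three methods, at 2 thresholds, gives 432 cases. In none is a method positive while R is negative.

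**Step 3: what the confidence limits would show.** For m successes out of m, the exact lower 95% limit is 0.025^(1/m). For assumed m:
- m = 60: 94.0%
- m = 100: 96.4%
- m = 140: 97.4%

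These limits depend on the number of men and on nothing else.

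**Step 4: relative sensitivity of the single methods.** Let s be the true sensitivity of the combined biopsy. Assume that disease found in cores is real. A method M nested in the combination then has reported sensitivity = true sensitivity / s. For an assumed s of 0.95, 1/s = 1.05; for 0.85, 1/s = 1.18. The overstatement is 5% to 18% in relative terms.

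**Step 5: illustration.** Assumptions: the methods err independently, there is no false-positive histology, and true prevalence is 40% to 60%. True NPV = (1 − prevalence) / [(1 − prevalence) + prevalence × (1 − s)].

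| Assumed true sensitivity SB / MR-TB / PET-TB | s | True NPV of PET/MR-TB | Reported sensitivity and NPV of PET/MR-TB | SOC sensitivity, true → reported |
|---|---|---|---|---|
| 60 / 75 / 75% | 1 − 0.40 × 0.25 × 0.25 = 97.5% | 96–98% | 100% | 90% → 92% |
| 40 / 50 / 50% | 1 − 0.60 × 0.50 × 0.50 = 85% | 82–91% | 100% | 70% → 82% |

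For SOC in the second row: 1 − 0.60 × 0.50 = 0.70, and 0.70 / 0.85 = 0.82.

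**Step 6: does the same factor apply to imaging?** No. Suppose 100 men truly have csPCA, the combined biopsy finds 90, and MRI is positive in 80 of those 90. The reported sensitivity is 80/90 = 88.9%. The true value depends on the 10 missed men:
- MRI positive in none: 80/100 = 80.0%, so the report is too high.
- MRI positive in 9: 89/100 = 89.0%, so there is practically no bias.
- MRI positive in all 10: 90/100 = 90.0%, so the report is too low.

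A suspicious lesion missed by its targeted cores is a case of the last kind. The bias for imaging can go either way.

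**The case against.** The strongest reply is that no reference standard is stated. The article condenses a fuller protocol, and an analysis plan may name one. That stands as a limit: the reference is inferred, and the identities assume the highest grade over all cores. A partial reference such as SB alone would break them, but would be incomplete in another way. The inference is still firm, because a prostatectomy or follow-up reference would contradict the day-21 timing printed in the article. The point concerns what is fixed, not what is left out.

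Second, the visit 5 section already plans to compare prostatectomy stage and grade with imaging and biopsy, outcome a already covers the added csPCA detection, and the highest Gleason score is recorded per method. This is true and makes the repair cheap. It does not change what outcome b would report.

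Third, the trial is exploratory, secondary endpoints are summarized descriptively, and the interim rule uses management change. This stands and limits the severity.

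Two stronger readings are tempting. A reader might infer that every sensitivity in outcome b, imaging included, is inflated by 5% to 18%. The factor needs the test to be nested in the reference; MRI and PSMA-PET/CT are not. A reader might also infer that prostatectomy plus follow-up would supply full accuracy. Whole-mount histology exists only in operated men, and re-biopsy is specified only under active surveillance, so biopsy-negative men are not systematically verified.

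**Conclusion.** The concern holds for the biopsy-method part of outcome b. On the stated timing, five of five measures for PET/MR-TB, and specificity and PPV for SB, MR-TB and PET-TB, are 100% before any data are seen. Sensitivity and NPV of the single methods and of SOC can fall below 100% but are relative to the combined biopsy. The sensitivities are overstated by 1/s, that is 5% to 18% if s lies between 0.95 and 0.85; that range is an assumption, as the article gives no value.

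The conclusion rests on two things: that day 21 allows no histology other than the cores, which the article's own dates show, and that the reference is the highest grade over all of them. MRI, PSMA-PET/CT and their scores share the imperfect reference but are not fixed at 100%, and the direction of their bias is unknown. The primary endpoint and its precision are unaffected. Severity is moderate.

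**What to change.** Change the wording in Table 1, Secondary outcomes and the analysis section {20a}:

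1. For the biopsy methods, drop specificity, PPV and accuracy against the combined biopsy. Report PCA and csPCA detection rates, with paired differences between methods and 95% confidence intervals.
2. Label sensitivity and NPV of SB, MR-TB, PET-TB and SOC as relative to the combined biopsy. Do not report them for PET/MR-TB.
3. Add a supplementary analysis at day 180: csPCA sensitivity and grade agreement of each biopsy method, PET/MR-TB included, against whole-mount histology in operated men. State that this is a selected, partially verified subset in which specificity and NPV cannot be reliably estimated.
4. Use the two-year follow-up, in which "PSA levels and PCA-specific diagnostic and therapeutic measures will be recorded quarterly", only to describe cancers detected later in biopsy-negative men.

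The data are already planned, so the cost is wording, a later read-out for item 3 and fewer headline accuracy figures.
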